### EuroQol (EQ-5D-3L)

The EQ-5D is a validated, generic patient-reported outcome measure covering five health domains (mobility, self-care, usual activities, pain/discomfort and anxiety/depression). We will use the original EQ-5D which contains three response options within each of the five domains [31, 32]. The use of this non-fracture-specific instrument will allow us to assess health-related quality of life outcomes in the health economic analysis. The EQ-5D has high validity and reliability in proximal humerus fractures [33] and hip fractures [34]. The EQ-5D is completed at baseline, 6, 12, 26 and 52 weeks.

### Bone union

The secondary outcome of bone union [35] is determined at 52 weeks (in line with the primary end point) using a CT scan and plain radiographs comprising posterior-anterior, lateral, semi 45° prone, semi 45°supine views and an elongated scaphoid view e.g. Ziter type view [36]. Union is defined as complete disappearance of the fracture line [3] on radiographs and complete bridging on CT scans [37–39] from those taken at baseline. We will identify partial union based on the proportion of the fracture plane traversed by bridging trabeculae on true sagittal and coronal formats of the scaphoid on CT. We are using CT to determine non-union as there is only poor to moderate inter-observer agreement (range of Kappa from 0.11 to 0.53) when determining the union of a scaphoid fracture on plain radiographs [40]. We will assess scaphoid fracture displacement on radiographs and on a CT scan [41] and determine malunion [42] on the 52 week CT scan (ratio of Scaphoid Height to Length ≥ 0.6) in the true sagittal axis of the scaphoid to assess any humpback deformity [43].

### Objective measures

We are measuring the range of movement [44] of both wrists using a goniometer and grip strength [45–48] of both hands using a calibrated Jamar dynamometer at baseline, 6, 12, 52 weeks and 5 years.

The measurements will be done with the subject seated, arm by the side, elbow bent at 90° and the wrist in neutral position for rotation [49]. The second setting on the Jamar dynamometer will usually be used but patients with large hands may need to use the third setting. This reflects common and evidence-based practice in assessing grip strength [50]. The Beighton Joint Laxity Score (excluding the thumb count for the injured wrist) will be recorded at baseline to measure hypermobility of joints [51]. These assessments will be standardised across participating sites using an instruction manual.

### Return to work and recreational activities

This will be established through patient self-report on the number of days off work and ability to perform usual activities when at work and when performing unpaid recreational activities. This will be recorded at 6, 12, 26 and 52 week follow-up.

### Complications

Expected and unexpected complications will be recorded at the 6, 12 and 52 week visit. The expected complications include:Infection, defined as for the “Surgical Site Infection” audit [52].Delayed wound healing, defined as any wound that has not healed by two weeks.Complex Regional Pain Syndrome (CRPS), defined as puffy painful swelling of the whole hand restricting full tuck of the fingers at 2 weeks.Nerve events (hypoaesthesia or numbness in the territory of the palmar cutaneous branch of the median nerve, superficial division of the radial nerve or the median nerve).Vessel events (large (>2 cm) haematoma in the line of the radial artery).Screw related complications (protrusion of either end into the adjacent joint, fracture or bending of the screw, a radiolucent halo around any part of the screw > 1 mm, screw backing out or moving).Degenerative change in the adjacent joints [53].Avascular necrosis (AVN) of the proximal pole of the scaphoid.

### Five year clinic review

The long-term consequences of cast immobilisation and internal fixation have not been adequately determined in RCTs. Therefore, at five years after their original injury, all remaining trial participants will be asked to attend a follow-up visit at a participating hospital for a clinical and radiographic follow-up. The clinical examination will include inspection and evaluation of scar sensibility when applicable, palpation for tenderness, measurement of joint movement with a goniometer, as well as measurement of grip strength and pinch strength [15].

Participants will complete a questionnaire that asks about perceived hand problems (e.g. weakness of wrist, reduced range of movement) as well as the primary outcome measure, the PRWE, and EQ-5D.

### Participant timeline

Figure 1 illustrates the process of enrolling participants into the study, the interventions being compared, and timing of assessments and hospital visits for the participants in the trial.

**Fig. 1 Fig1:**
[figure not shown]
Flow of participants in the SWIFFT trial

### Sample size

For surgery to justify its increased costs and the exposure to risk, it must result in greater or quicker improvement in patients’ wrist symptoms and function compared with non-operative management. We judge that a 6 point improvement in the PRWE in the surgery group (compared to the controls) would be a minimal clinical important difference. We estimate the standard deviation of PRWE at 52 weeks to be 20 points from the PRWE User manual [54]. This figure is reported for distal radius fracture rather than scaphoid fracture at 6 months. The only published evidence for scaphoid fracture implies a standard deviation in the range of 8 to 10 points [15]; however, this estimate was at a median of ten years after the patient’s injury. To be conservative we have chosen the estimate of standard deviation to be 20, which gives a standard effect size of 0.3 for the 6 point PRWE difference.

We will use a superiority design to observe an effect size of 0.3 at 80 % power using a 2-sided 5 % significance level requiring 350 participants in total. After allowing for 20 % attrition we need to recruit and randomise 438 participants (219 surgery and 219 controls). The estimate of attrition is likely to be realistic given that four RCTs (three studies were single centre and one study had two centres) included in a systematic review of the treatment of scaphoid fractures found response rates for completion of patient-reported functional outcomes between 77 and 100 % [12].

To minimise attrition we will exclude the rare patient in this population who lacks mental capacity and therefore unlikely to comply with treatment or data collection. Active and systematic follow-up of all randomised participants will be conducted at 6, 12, 26 and 52 weeks when we will arrange for the questionnaire to be completed when the participant attends the clinic. An additional 5 year review is also planned. We will monitor the completion of questionnaires at clinics and share retention figures with each trial site blinded by centre.

At 52 weeks a £40 payment will be made to patients who attend the clinic. Concurrently we will employ a proven postal strategy for the return of questionnaires. This will include the use of reminder letters after 2 and 4 weeks and the option for completion of an abridged questionnaire (a minimum of the primary outcome and EQ-5D) via telephone after 6 weeks. At 52 weeks only (the primary time-point for the study), in addition to the 6 week telephone call we will write to non-responding patients to ask them to complete the PRWE to help maximise return of the primary outcome. We will still call the patient to complete the remainder of the questionnaire over the telephone. At 26 weeks, when the patient does not need to attend for a hospital appointment, we will include an unconditional incentive payment of £5 with the postal questionnaire. We will also circulate a regular newsletter and update the trial website (http://www.swifft.co.uk/), to keep the participants informed of study progress and engaged with the trial. A trial ‘tagline’ will be placed on postal envelopes to patients to highlight the importance of patients’ involvement in the research. At the five year follow-up, participants will receive £80 to attend hospital for their clinic review which should cover time off work, travel and parking costs. Finally, to minimise attrition bias, as there is randomised evidence in a recent systematic review that the return of postal questionnaires can be improved when patients are included in a prize draw [55], those patients who return the questionnaire at 26 weeks could win an iPad worth £500. When patients attend their hospital clinic appointment at 52 weeks and 5 years, they will be entered into additional prize draws to win an iPad worth £500.

### Recruitment

Strategies for achieving adequate participant enrolment to reach target sample size include seeking advice from our patient focus group, sharing best practice with our Research Nurses, and bi-annual discussion with our Principal Investigators at the scientific meetings of the BSSH. Table 4 shows the project plan and milestones.

**Table 4 Tab4:** Time schedule of the study project plan

Time period (month)	Activity
1–3	Complete local R&D approval and set up for 4 sites
4–6	Initiate early recruitment (internal pilot study at 4 sites and continue R&D approval for other sites)
7–36	Main recruitment for trial
37–48	Complete final 12 month follow-up
49–54	Analysis and write up of main HTA monograph
55–63	Preparation for 5 year clinic review
64–96	Conduct 5 year clinic review
64–69	Internal pilot follow-up for 5 year review
70–72	Three months to follow-up the last participant to be followed-up for the internal pilot
73–75	If internal pilot is unsuccessful, to complete analysis and write up the report
97–105	Allow 9 months to complete clinics and prepare analysis
106–108	Complete analysis and write HTA addendum monograph

Hospital staff will be provided with training at the Site Initiation Visits and a Trial Site Manual to ensure adherence to the delivery of the interventions in the trial. During the trial, training and reminders will be implemented using e-mail bulletins, face-to-face meetings with the PI’s at BSSH conferences and a training day with Research Nurses. In addition the Trial Co-ordinators will provide support and guidance to staff when required (e.g. when new staff join or replace existing site staff) and will seek clinical guidance from the CI when necessary.

To assess adherence with the trial protocol, sites will be asked at the 6 and 12 week hospital visits to complete a ‘Treatment Confirmation Form’. This will be used to record the treatment that the patient received after randomisation and reasons for any change in treatment. It also asks whether non-union is suspected for patients randomised to conservative treatment. This will allow the trial team to check with the hospital site that surgical fixation is being offered to these patients. Trial participants are also asked at their 12 week follow-up how many of the home exercises they have performed and how useful they found the leaflet detailing exercises they need to perform for rehabilitation.

### Randomisation

The Research Nurse will identify potentially eligible patients presenting in Accident and Emergency (A&E) Departments, or referred from various sources (e.g. walk-in centre, cottage hospital), and at fracture clinics. The orthopaedic surgeon will confirm eligibility and invite the patient to consider joining the study. The Research Nurse or clinician will then provide an information sheet and answer any questions. The patient will be asked whether they agree to consent at that time or are offered up to 48 h to discuss the study and their participation with family or friends before deciding.

When patients have given consent their baseline forms will be completed and randomisation done. The Research Nurse or recruiting clinician will contact York Trials Unit, either by telephone or via the internet, to access the secure randomisation service. This will ensure treatment concealment and unbiased allocation. Once eligibility is confirmed, patients will be randomised (via a secure, computer generated allocation sequence) to receive immediate surgical fixation or immobilisation of the wrist in a cast.

Patients and their clinician will be informed of the allocations. As the trial is pragmatic and compares surgery with initial cast treatment, blinding of participants and clinicians to treatment allocation is not possible. When possible, the surgeon will take no part in the postoperative subjective assessment of patients. The statistical analysis will also be performed blind as far as possible. We will mitigate against bias by ensuring that all radiographs and CT scans are assessed by two independent consultant musculoskeletal radiologists and a consultant orthopaedic surgeon.

As the non-union rate for displaced fractures is 14 % compared with 10 % for transverse undisplaced fractures [3, 5, 56], randomisation will be stratified by the presence or not of displacement of a scaphoid fracture as seen on radiographs [5, 56] Within strata, a sequence of confidential random block sizes will be used to generate the block allocation sequence. To avoid predictability of the randomisation we will not stratify by site. The radiographic views to assess displacement should include the semi 45° prone, semi 45°supine and an elongated scaphoid view e.g. Ziter [36] type view (Fig. 2). Displacement is defined as a step greater than 1 mm and less than or equal to 2 mm or a gap greater than 1 mm and less than or equal to 2 mm as seen on the radiographic views. This magnitude of displacement will avoid compromising surgeon equipoise for non-operative treatment as displacement >2 mm suggests significant instability and therefore the need for surgical intervention.

**Fig. 2 Fig2:**
[figure not shown]
Radiographic views of a scaphoid fracture. Four radiographic views shown here, and a fifth elongated scaphoid view, establish the presence of a “clear” and ”bicortical” fracture of the waist of the scaphoid. Such patients are eligible for the SWIFFT trial. These radiographs also help determine whether the fracture is displaced for blocked randomisation after obtaining consent

### Data management

Case Report Forms will be used to record all the information required from the protocol. Essential Trial documentation which individually and collectively permits evaluation of the conduct of a clinical trial and the quality of the data produced will be kept within the Trial Master File and Investigator Site Files. The Sponsor will ensure that this documentation is retained for a minimum of five years after the conclusion of the trial and a minimum of 20 years in electronic format in accordance with guidelines on Good Research Practice. Paper data will then be disposed of securely and electronic data will be anonymous of identifiable information.

All study-related information will be stored securely in the co-ordinating centre at the University of York or at an alternative secure off-site facility. All electronic records will be stored on a password-protected server. All participant data will be identified by a coded ID (identification) number to maintain participant confidentiality. All participant information will be stored in locked cabinets in areas with restricted access. Data on trial participants’ X-rays and CT scans will be stored securely at The University Hospitals of Leicester NHS Trust. Participants’ data may be reviewed by authorised persons on the research team or other authorised people to verify that the study is being carried out correctly all of whom will have a duty of confidentiality. Trial participants will give permission for this authorised review of their data at the time of consent. All names and other identifying information will be removed before the data is analysed and the results presented to the medical community at conferences and in scientific journals.

The Data Monitoring and Ethics Committee (DMEC) will be the only body to have access to the unblinded comparative data from the trial. The role of its members is to monitor these data and make any recommendations to the Trial Steering Committee (TSC) on whether there are any ethical or safety reasons why the trial should not continue. The TSC will provide overall supervision for the trial on behalf of the Sponsor and Funder.

### Statistical analysis plan

A detailed analysis plan will be agreed with the Data Monitoring and Ethics Committee at an early stage of the study, before all of the data has been collected. Any subsequent amendments will be clearly stated and justified. All analyses will be conducted on an intention to treat basis, including all available randomised participants in the groups to which they were allocated. Analyses will be conducted using 2-sided significance tests at the 5 % significance level (unless otherwise stated). The statistician conducting the analyses will remain blind to treatment group until all data summaries and results are finalised. For some variables the type of data reveals treatment allocation (e.g. complication data), hence relevant analyses will be conducted by a second statistician.

The flow of participants through each stage of the trial will be presented in a CONSORT flow diagram [57]. PRWE scores will be summarised descriptively (number, mean, standard deviation, median, interquartile range, minimum and maximum) at each time point by treatment group and overall. PRWE at baseline will be collected for the time before and after injury. Mean pre-injury PRWE scores will be presented in total and for each treatment group and compared descriptively to PRWE scores post-injury at baseline and all other follow-up time points.

Our primary analysis will compare total PRWE scores between treatment groups at 52 weeks using a covariance pattern mixed model incorporating all post-randomisation time points, where effects of interest and baseline covariates are specified as fixed effects, and the correlation of observations within patients over time (random effect) is modelled by a covariance structure. The outcome modelled will be PRWE at 6, 12, 26 and 52 weeks, predicted by treatment group, time, treatment group-by-time interaction and adjusting for age, fracture displacement (undisplaced vs. minimally displaced) and hand dominance. Estimates of the difference between treatment groups in total PRWE scores will be derived at all time points with 95 % confidence intervals and *p*-values. The primary end point will be the treatment effect estimate at 52 weeks. This model will naturally include all patients who provide data for the baseline covariates, and valid PRWE data for at least one post-randomisation follow-up time point.

The impact of missing PRWE outcome data will be minimised to some extent by using the mixed model, which allows the inclusion of intermittent responders in the primary analysis. PRWE scores for complete and intermittent responders will be compared descriptively. The impact of missing data will additionally be assessed using multiple imputation by chained equations. Missing outcome and covariate data will be predicted by age, fracture displacement, hand dominance, available PRWE data at other follow-up time points, and any baseline covariates found to be predictive of missing 12 month outcome data.

All secondary outcomes will be summarised descriptively. The following outcomes will be analysed using the same methods as the primary analysis adjusting for the same covariates: pain and disability subscales of the PRWE, physical health and mental health component summaries of the SF-12 and range and grip strength. Where available, baseline values of the dependent variable will also be included as a covariate in the models. The presence of any complication assessed by clinical examination up to 52 weeks will be analysed by logistic regression (sufficient numbers permitting). Complications will be defined as medical, surgical or plaster cast related. Union will be assessed as a percentage (0–100 %) and categorised as: total non-union [0 %]; slight union [>0–20]; partial union [>20–70]; mostly united [>70–<100]; and complete union [100 %]. Summary statistics for union will be presented at each time point by trial arm. Union will be dichotomised into a ‘Probably need surgery’ group [0–20 %] and a ‘Probably do not need surgery’ group [>20–100 %] and analysed using a logistic regression adjusting for treatment group.

Two subgroup analyses will be undertaken: one exploring patient preferences (surgery, plaster cast, no preference) and the second exploring the type of fracture displacement (undisplaced, displaced), for any differential effect of the trial treatments in these subgroups. Each baseline factor (preference or displacement) and its interaction with the randomised treatment group will be added to the primary analysis model. Our expectation is for patients who preferred surgery to benefit more from surgery over plaster cast treatment and conversely for patients who preferred plaster cast to benefit more from plaster cast than surgery. For patients with a displaced fracture we expect them to benefit more following surgery than patients whose fracture is undisplaced. Since the trial is not powered for these subgroup analyses, any inferences will be made with caution.

The number of adverse events experienced by each participant and the total number of events overall will be summarised for each treatment group.

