### Patient rated wrist evaluation

The PRWE is completed at baseline for the time before and after injury, and at 6, 12, 26, 52 weeks and 5 years after randomisation. The PRWE is a 15-item questionnaire that is completed by the patient. It is a brief, reliable and valid instrument for assessing wrist pain and disability [28, 29]. Scoring for all the questions is on a 10-point, ordered scale ranging from ‘no pain’ or ‘no difficultly’ (0) to ‘worst ever pain’ or ‘unable to do’ (10). Two non-overlapping subscales are generated: pain and function and a total score can be computed on a scale of 0 to 100 (0 = no disability) where pain and function domains are weighted equally.

PRWE has been chosen as the primary outcome as patient reported functional outcomes are favoured for decision making and it allows assessment of both wrist pain and function.

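### The primary model omits baseline PRWE, which is collected before randomisation and whose subscales are adjusted for their own baseline; precision may be lost and no reason is given

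*Protocol article*

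**What the plan says.** Under the heading Patient rated wrist evaluation, the protocol article states: "The PRWE is completed at baseline for the time before and after injury, and at 6, 12, 26, 52 weeks and 5 years after randomisation". According to the Randomisation section, baseline forms are completed after consent and before allocation, so these scores are legitimate covariates.

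The Statistical analysis plan section gives the terms of the primary model. "The outcome modelled will be PRWE at 6, 12, 26 and 52 weeks", explained by treatment, time, "treatment group-by-time interaction and adjusting for age, fracture displacement (undisplaced vs. minimally displaced) and hand dominance". Baseline PRWE is thus neither a covariate nor a modelled time point. Its stated use is a summary in which pre-injury scores are "compared descriptively to PRWE scores post-injury at baseline and all other follow-up time points".

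The same section then turns to the secondary outcomes. Several are to be "analysed using the same methods as the primary analysis adjusting for the same covariates: pain and disability subscales of the PRWE", together with the SF-12 components, range of movement and grip strength. It adds: "Where available, baseline values of the dependent variable will also be included as a covariate in the models".

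On how the total relates to its parts, the article says that "a total score can be computed on a scale of 0 to 100 (0 = no disability) where pain and function domains are weighted equally".

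**The concern.** The baseline value of an outcome is an obvious candidate covariate in a model for that outcome. Here it is collected and is applied to the two subscales, but not to their total, which is the primary outcome.

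Two things are at stake. If baseline PRWE predicts 52-week PRWE beyond the covariates already in the model, leaving it out keeps explainable variance in the error term, and a chance imbalance in wrist status between the arms is left uncorrected. Also, the total and its subscales would be estimated with different covariate sets. If they appeared to disagree, a reader could not tell how much of the disagreement came from the adjustment.

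**Working it through.** **Inputs.** From the Sample size section: difference 6 points, SD 20, two-sided 5%, power 80%, 350 analysed, 20% attrition, 438 randomised in equal arms. The correlation rho between baseline and 52-week PRWE is not in the document. It is assumed here, and it should be read as a partial correlation, given the covariates already in the model.

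**Step 1: reproduce the plan's figure.** Per arm, n = 2 × (1.96 + 0.8416)² × (20/6)² = 174.4, rounded up to 175, so 350 in total. Allowing for attrition, 350/(1 − 0.20) = 437.5, rounded up to 438. Both figures reproduce with no baseline adjustment. Power at 175 per arm is 80.1% by the normal approximation and 79.9% by the noncentral t.

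**Step 2: effect of adjustment.** Adding the covariate multiplies the residual variance by 1 − rho², so:

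- residual SD = 20 × √(1 − rho²)
- noncentrality = (6 / residual SD) × √(175/2), on 348 degrees of freedom
- 95% half-width = 1.96 × residual SD × √(2/175)

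| Assumed rho | Residual SD | Power at 350 (noncentral t) | 95% half-width, points |
|---|---|---|---|
| 0 | 20.0 | 79.9% | 4.19 |
| 0.1 | 19.9 | 80.3% | 4.17 |
| 0.2 | 19.6 | 81.5% | 4.11 |
| 0.3 | 19.1 | 83.5% | 4.00 |
| 0.4 | 18.3 | 86.3% | 3.84 |

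For example, at rho = 0.3 the residual SD is 20 × √0.91 = 19.08, and the half-width is 1.96 × 19.08 × √(2/175) = 4.00. The power gain over no adjustment runs from 80.3 − 79.9 = 0.4 percentage points at rho 0.1 to 86.3 − 79.9 = 6.4 at rho 0.4.

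This is a two-group calculation at one visit, as in the plan's own sample size. It approximates the repeated-measures model and is not a simulation of it.

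**Step 3: covariate rules side by side.**

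| Outcome | Age, displacement, hand dominance | Own baseline value |
|---|---|---|
| PRWE total (primary) | yes | no |
| PRWE pain and function subscales | yes | yes, where available |

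The subscales come from the same 15-item form as the total, so if one baseline is available, so are the others. With two baseline scores on file, the subscale rule also leaves open which one counts as the baseline value.

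**The case against.** The strongest reply is that nothing here is invalid. Leaving a prognostic covariate out of a model does not bias a randomised comparison, and the sample size was calculated without it. Both points stand. A reader might infer that the primary estimate is biased or that the trial falls short of its 80% power; the document supports neither.

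The gain is also unproven. One baseline score describes the wrist before injury in a young, active population and may sit near zero. The other describes the acute state within about two weeks of fracture, a year before the endpoint. Either may predict 52-week PRWE weakly, and at rho 0.1 to 0.2 the benefit is small. This stands too, which is why the figures are a range. By the same token, a chance imbalance reaches the estimate only in proportion to the regression slope of outcome on baseline, which is unknown. Its expectation is zero, and the confidence interval already allows for it. Displacement, the severity factor that the trial regards as prognostic, is both stratified and adjusted for.

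A reader might further infer that the total and subscale effects ought to sum and that baseline adjustment would make them do so. It would not. Each would still be adjusted for a different baseline variable, and with missing visits and separately fitted covariance structures exact additivity need not hold.

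Finally, the detailed analysis plan is not shown. It may well settle which baseline score is meant and how gaps are filled. It does not remove the point, because the article itself fixes the primary covariate list and a different rule for the subscales. If the baseline sentence was meant to cover the primary model as well, it conflicts with that list, and the two need reconciling.

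**Conclusion.** The point holds as a matter of efficiency and consistency. The primary outcome receives a weaker adjustment than its own components, without explanation, although the data for the stronger adjustment are collected before randomisation.

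The size depends wholly on an assumed partial correlation. Over 0.1 to 0.4, power at 350 analysed would be about 80.3% to 86.3% instead of about 80%. If the correlation is near zero, essentially nothing is lost by the omission and essentially nothing by correcting it. The change is worth making on that balance, but the validity of the primary analysis does not depend on it.

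**What to change.** In the primary model, add baseline PRWE as a fixed covariate with a baseline-by-time term, so that its slope may differ between visits. Name the score used: post-injury, pre-injury or both. Apply the same rule, with the same choice of score, to the total and the subscales.

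State how missing baselines are handled. The article's model includes only patients with baseline covariate data, so a new covariate could otherwise drop people. Mean imputation of the baseline value would keep them, as would a model that treats baseline as an outcome with the arm means constrained equal.

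No new data are needed. The cost is four parameters per baseline score (one slope for each of the four visits) and a few sentences in the plan. The gain is possible added precision, protection against chance imbalance and one covariate rule throughout. The article says that the detailed plan will be agreed before all data are in, so the choice can be made there without sight of results. If the sponsor prefers to keep the present model, a stated reason for treating the total and the subscales differently would at least remove the inconsistency.

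### The listed predictors for the multiple imputation leave out randomised treatment, so the missing-data check on the 52-week PRWE effect can be biased if followed as written

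*Protocol article*

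**What the plan says.** All of the relevant text is in the Statistical analysis plan section of the protocol article.

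- **Primary model.** PRWE at 6, 12, 26 and 52 weeks is "predicted by treatment group, time, treatment group-by-time interaction and adjusting for age, fracture displacement (undisplaced vs. minimally displaced) and hand dominance". Patients enter if they have the baseline covariates and at least one valid follow-up PRWE.
- **Missing-data check.** "The impact of missing data will additionally be assessed using multiple imputation by chained equations".
- **Imputation predictors.** "Missing outcome and covariate data will be predicted by age, fracture displacement, hand dominance, available PRWE data at other follow-up time points". To these the article adds whichever baseline variables turn out to predict a missing one-year score.
- **Further detail.** "A detailed analysis plan will be agreed with the Data Monitoring and Ethics Committee at an early stage of the study". That document is not at hand.

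The imputation list repeats all three adjustment covariates of the primary model. It names neither treatment group nor imputation by arm.

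**The concern.** An imputation model should contain at least the terms of the analysis it feeds. When the exposure whose effect is being estimated is left out, the imputed values are drawn as if, given the other predictors, the arms did not differ. The imputed 52-week scores then reflect treatment only so far as PRWE at other visits carries it, and the effect at 6 or 12 weeks may be quite unlike the effect at 52 weeks.

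The problem is sharpest for patients with no follow-up PRWE. The mixed model leaves them out and imputation can bring them in, but the listed predictors give their scores no treatment difference at all.

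What is at stake is how the check is read. A gap between the imputed and primary estimates could be taken as evidence about attrition when it comes from the imputation model.

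**Working it through.** **Inputs from the article (Sample size section).** Target difference: "We judge that a 6 point improvement in the PRWE in the surgery group". SD: "we have chosen the estimate of standard deviation to be 20". Power is 80%, the two-sided level 5%, and attrition 20%.

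**The plan's own figure.** Per arm, 2 × (1.960 + 0.842)² × 20² / 6² = 174.4, so 175 per arm and 350 in total; 350 / 0.8 = 437.5, so 438. The sample size reproduces. The article gives no figure for the imputation analysis itself.

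**Assumptions not in the article.** Between-visit correlation ρ of 0.3 to 0.8, equal for all pairs of visits unless stated; 20% missing at 52 weeks, completely at random and equally in both arms; the effect profiles shown below.

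**Formula.** Let m be the fraction missing at 52 weeks, δ52 the true effect there, δk the effect at earlier visit k, and bk the pooled regression coefficient of 52-week PRWE on visit k with treatment left out. In large samples the imputed analysis estimates

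(1 − m) × δ52 + m × Σ bk δk.

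**No earlier PRWE among the missing, true effect 6.** The second term is zero: 0.8 × 6 = 4.8, a shortfall of 1.2 points (20%). At 30% missing it would be 0.7 × 6 = 4.2.

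**Constant effect of 6, only week 52 missing.** Pooling the arms adds 6²/4 = 9 to every variance and covariance, so each b = (400ρ + 9) / [409 + 2(400ρ + 9)].

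- ρ = 0.3: b = 129/667 = 0.193; transmitted effect 3 × 0.193 × 6 = 3.48; estimate 4.8 + 0.2 × 3.48 = 5.50.
- ρ = 0.6: b = 249/907 = 0.275; transmitted 4.94; estimate 5.79.
- ρ = 0.8: b = 329/1067 = 0.308; transmitted 5.55; estimate 5.91.

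**Simulation.** Chained equations on four visits, 438 patients, SD 20, 20% missing, 250 trials per cell (simulation standard error 0.10 to 0.15). Each cell gives the 52-week estimate at ρ = 0.3 / 0.6 / 0.8.

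| Effect at 6, 12, 26, 52 weeks | Missing pattern | Treatment omitted | Treatment included |
|---|---|---|---|
| 6, 6, 6, 6 | all visits | 4.84 / 4.86 / 4.67 | 6.08 / 6.08 / 5.54 |
| 6, 6, 6, 6 | week 52 only | 5.41 / 5.65 / 6.25 | 5.88 / 5.86 / 6.36 |
| 0, 2, 4, 6 | week 52 only | 5.03 / 5.13 / 5.33 | 6.02 / 6.02 / 6.12 |
| 15, 10, 7, 6 | week 52 only | 6.02 / 6.59 / 6.63 | 6.03 / 6.12 / 5.97 |
| 15, 8, 3, 0 | week 52 only | 0.80 / 1.51 / 1.27 | −0.09 / 0.27 / 0.05 |
| 15, 8, 3, 0 | all visits | 0.12 / 0.02 / −0.11 | 0.22 / 0.04 / −0.19 |

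In the constant-effect rows at ρ = 0.8 the column with treatment is itself off 6 (5.54 and 6.36). This is simulation error and, with all visits missing, slow convergence of the chains, so the two columns should be compared with each other there. For the early-only profile with week 52 missing, the formula gives 0.85, 1.20 and 1.25, so the simulated 1.51 includes some noise. A similar profile (15, 10, 4, 0) in a large-sample simulation, with equal correlation 0.5 or first-order autoregressive correlation 0.6, gave 0.4 to 1.3.

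**Scale.** The planned standard error of the difference is 20 × √(2/175) = 2.14 points, so a bias of 1.2 is 1.2 / 2.14 = 0.56 of a standard error and one fifth of the 6-point target.

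**The case against.** The strongest reply is that this is a condensed article. It defers detail to an analysis plan that is not shown, does not call its list exhaustive and does not say the arms are pooled, so treatment may be handled there. That stands as a limit: the bias is conditional on the list being followed as written. It does not remove the point, because the article chose to specify the imputation model. The clause on baseline variables predictive of missingness does not supply treatment either. The section distinguishes effects of interest from baseline covariates, and the clause admits only variables found to predict missingness. Elsewhere the section names treatment group when it is meant, as in the union and subgroup analyses.

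The second reply is that the larger biases need unlikely conditions. The Timing of primary outcome section reports little change between 26 and 52 weeks in two small trials, which argues against an effect first appearing at 52 weeks. The Sample size section describes active follow-up at earlier visits, so many patients missing at 52 weeks should have earlier scores. This also stands: for a constant effect with only week 52 missing, the shortfall is about 0.1 to 0.6 points.

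Three stronger inferences are tempting and unsupported:

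- **That the bias always runs towards no difference.** The 15, 10, 7, 6 profile gives no bias or an upward one.
- **That the check cannot test the primary result.** With no effect at any visit, leaving treatment out biases nothing, and imputation still brings in patients whom the mixed model drops.
- **That the article expects an early-only effect.** The Background reports earlier return of function and says longer-term benefit could not be established. It does not predict a null result at 52 weeks.

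**Conclusion.** The point holds in a limited form. The stated imputation predictors omit randomised treatment and so do not match the treatment and treatment-by-time analysis they are meant to check. Followed literally with pooled arms, they give a sensitivity estimate that is generally biased when an effect exists at any visit.

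With SD 20, 20% missing completely at random and correlations of about 0.3 to 0.8, the loss is at most about 1.2 points of a true 6 in the profiles examined, and about 5.4 to 5.9 is recovered when the effect is constant and only week 52 is missing. A purely early effect leaves a spurious 0.4 to 1.5 points when earlier visits are observed. The correlations and profiles are assumptions, and the size grows with the missing fraction.

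A reader might infer that the trial's main result is at risk. It is not: the primary mixed model includes treatment and treatment-by-time and does not use the imputed data. Nor is imputation the only look at missing data, since a descriptive comparison of complete and intermittent responders is also planned. Severity is moderate or minor.

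**What to change.** Add treatment group to the imputation model, preferably by imputing separately within each arm so that treatment-by-time is preserved. If the full analysis plan already does this, say so and correct the list. A masked arm code is enough, so the statistician can stay blind as planned. The cost is one line of wording and minor programming; no new data are needed.
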